### Recruitment

First, the medical staff is informed about the goal and procedure of the study. Second, the medical staff (physicians) of each psychogeriatric unit of the eight nursing homes selects eligible residents with dementia and NPS who have a referral for individual music therapy. Third the researcher provides an information letter with informed consent form to competent residents and to legal representatives of non-competent residents. After informed consent or proxy informed consent has been given and the participant has been recruited, the participants are randomly allocated to the intervention group (individual music therapy) or control group (individual attention).

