### Secondary outcomes measures

Secondary outcomes are also assessed in all /participating residents and include pain, quality of life, neuropsychiatric symptoms (agitation, anxiety, symptoms of depression), quality of sleep and psychotropic drug use.

**Pain** will be assessed by a blinded research assistant at baseline, six weeks and twelve weeks during 2 min before and after the intervention session or individual attention with the PAIC-15 (Pain Assessment in Impaired Cognition) [54, 55] which is an observational assessment instrument that lists 15 items and uses scores from 0 to 3 for each item. PAIC-15 comprises three domains: facial expression, body movements and verbalizations/vocalizations. Each domain has 5 items and the total score is the sum of all items, ranging from 0 to 45. The research assistant will be trained in using the PAIC-15.

**Quality of life** will be rated by non-blinded nurses at baseline (T0), at six weeks (T1) and at twelve weeks (T2) with the Quality of Life in Late-Stage Dementia Scale (QUALID) [56] that can be used with late-stage dementia patients in institutional settings and has been designed for proxy-rating by nurses. Responses reflect patient behavior over the past seven days. The QUALID consists of eleven items that are short and simple and is characterized by a good reliability and validity and the Dutch translation was a valid measure for quality of life in patients with advanced dementia [57]. The total score is the sum of all items, ranging from 11 to 55. Lower scores indicate a higher quality of life.

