**Neuropsychiatric symptoms (NPS)** will be assessed by non-blinded nurses at baseline (T0), at six weeks (T1) and at twelve weeks (T2) with the Neuropsychiatric Inventory Nursing Home Version (NPI-NH), a scale originally developed by Cummings [33, 34] to assess NPS in outpatients with dementia. The nursing home version was developed for use of professional caregivers in institutions and proved to be valid and reliable for trained nursing staff [58, 59]. The NPI-NH is the only nursing home instrument to assess NPS that occurred in the past four weeks that has been translated into Dutch [60]. The NPI is a structured interview that includes 12 neuropsychiatric symptoms: delusions, hallucinations, agitation, depression, anxiety, euphoria, apathy, disinhibition, irritability, aberrant motor behavior, night-time disturbances and appetite/eating change. Frequency (F) and severity (S) of each symptom are rated on a four (1–4) and three (1–3) point scale respectively. A separate score can be calculated for each symptom by multiplying the frequency and severity (FxS score), resulting values range from zero to 12 for each symptom. Summing all FxS scores results in a total score that ranges from 0 to 144. Interview also includes a caregiver distress questions using a 5-point scale.

**Agitation and aggression** will be assessed by non-blinded nurses at baseline (T0), 6 weeks (T1) and 12 weeks (T2) using the caregiver rated questionnaire Cohen-Mansfield Agitation Inventory (CMAI). This instrument, developed by Cohen-Mansfield and Billig [61] and validated by Miller [62] is an instrument that specifically addresses agitation or aggression that has been translated into Dutch. The Dutch translation of the CMAI (CMAI-D) has been validated by De Jonghe [63] and rated agitated behaviors occurred during last two weeks. The frequency of each symptom is rated on a seven-point scale (1–7) ranging from ‘never’ to ‘several times an hour’. Summing all symptom scores results in a total score that ranges from 29 to 203.

**Depression** will be rated by non-blinded nurses at baseline (T0), at six weeks (T1) and twelve weeks (T2) with the Cornell Scale for Depression in Dementia (CSDD) [64], which has good internal consistency [65]. Responses reflect symptoms of depression in the week before. The CSDD is a 19-item instrument, with scores for each item ranging from 0 to 2 (total score range 0–38). The CSDD has been translated into Dutch [66].

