### Participants timeline

All eligible residents for whom consent have been provided will be randomly allocated to the intervention group (individual music therapy) or control group (individual attention). Randomization will take place with a statistician using randomization software. The outcomes variables are measured at baseline (T0) one week before individual attention of music therapy starts (pre-treatment), after 6 weeks of intervention (T1) and after 12 weeks of intervention (T2). Figure 1 shows the participant’s flow.

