**Fig. 1 Fig1:**
[figure not shown]
Participant flow: T0 baseline data collection, T1 follow up assessment at 6 weeks and T2 the follow up after 12 weeks. Participants who are lost to follow-up at the T2 assessment can still be included in the analyses, due to the use of mixed models analyses

Measurements (DS-DAT and PAIC-15) will be done at baseline T0, just shortly before (T1a and T2a) and shortly after the intervention (T1b and T2b); to assess overall effects, cumulative and immediate effects (**see** Table 1). An independent research assistant performs the blinded direct observations and complies the primary outcome well-being (measured with the DS-DAT) and secondary outcome pain (measured with the PAIC-15). The nursing staff will complete the unblinding observations scales concerning the various stages of dementia at baseline T0 and they will fill in the unblinding questionnaires about QoL, NPS, agitation and symptoms of depression at T1b and T2b.

Data prescription records concerning medication use, among which psychotropic drugs, will be extracted from the electronic medical charts by [name], physician employed by the participating organization.

**Table 1 Tab1:** Instruments at different assessment moments

Outcomes/instruments	T0 week 0	T1a (pre-treatment) Week 6	T1b (post-treatment) Week 6	T2a (pre-treatment) Week 12	T2b (post-treatment) Week 12
Primary outcome					
Well-being (DS-DAT)	X	X	X	X	X
Secondary outcomes					
Pain (PAIC-15)	X	X	X	X	X
Quality of life (QUALID)	X		X		X
Neuropsychiatric symptoms (NPI-NH)	X		X		X
Agitation (CMAI)	X		X		X
Depressive symptoms (CSDD)	X		X		X
Stages of dementia (GDS)	X				
Rest/activity (Actigraphy)	X				X
Medication use (ATC classification)	X				X

DS-DAT: Discomfort Scale - Dementia of Alzheimer Type, PAIC-15: Pain Assessment in Impaired Cognition, QUALID: Quality of Life in Late-Stage Dementia Scale, NPI-NH: Neuropsychiatric Inventory Nursing Home Version, CMAI: Cohen-Mansfield Agitation Inventory, CSDD: Cornell Scale for Depression in Dementia, GDS: Global Deterioration scale, ATC: Anatomical Therapeutic Classification system

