#### Blinding

The study is single blinded, i.e. that the therapist and the patients themselves are not blinded. Trained research assistants who are blinded to intervention assignment, conduct the well-being (primary outcome) and pain (secondary outcome) measurements. The nursing staff completes the scales concerning the stage of dementia, QoL, NPS, agitation and symptoms of depression. Blinding to these measurements is not possible because these measurements require familiarity with the person’s usual behavior in the previous week(s). The nursing staff who complete the questionnaires are not blinded to intervention assignment, but they are not informed about the hypothesis and specific research questions.

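### Nurse-rated baseline scales are open to knowledge of the allocation, because the text does not say that allocation is withheld until they are complete

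*Protocol article*

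**What the plan says.** **Order of steps.** Recruitment states: "After informed consent or proxy informed consent has been given and the participant has been recruited, the participants are randomly allocated". Participants timeline repeats the order: "All eligible residents for whom consent have been provided will be randomly allocated to the intervention group". It then describes the assessments: "The outcomes variables are measured at baseline (T0) one week before individual attention of music therapy starts (pre-treatment". T0 is thus tied to the first session, not to randomisation. Neither section says that T0 comes before allocation, or that allocation is held back until T0 is done.

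**Who rates at T0.** Secondary outcomes measures says of QUALID that it "will be rated by non-blinded nurses at baseline (T0), at six weeks (T1) and at twelve weeks (T2"), of NPI-NH that it "will be assessed by non-blinded nurses at baseline (T0), at six weeks (T1) and at twelve weeks (T2") and of CMAI that it "will be assessed by non-blinded nurses at baseline (T0), 6 weeks (T1) and 12 weeks (T2"). The CSDD entry is worded in the same way. The text below Fig. 1 says of GDS: "The nursing staff will complete the unblinding observations scales concerning the various stages of dementia at baseline T0". Blinding adds: "The nursing staff who complete the questionnaires are not blinded to intervention assignment". It gives as the reason that the ratings need familiarity with the resident's usual behaviour, and it notes that nurses are not told the hypothesis. DS-DAT and PAIC-15 are rated by a blinded research assistant at every assessment, T0 included.

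**How T0 is used.** Under Data analysis, overall effects take the post-session value as outcome and adjust for baseline. Table 1 gives the four nurse-rated outcomes no pre-session assessment at weeks 6 and 12, so the overall effect is the only one of the three defined effects that can be estimated for them. The adjusted models also include cognitive deterioration, for which GDS is the only instrument described.

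**The concern.** Adjusting for baseline gives an unbiased treatment effect when the baseline is independent of allocation. That holds by design if the baseline is recorded before anyone involved knows the arm. It is no longer guaranteed if the rater knows the arm when filling in the form.

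Here the rater is a nurse on the ward, and Recruitment says residents are selected with a referral for music therapy. A nurse might score a resident as more troubled when music therapy is coming, or when it has just been denied. Higher scores are worse on all four scales. If the music therapy arm is scored too high at T0, an adjusted analysis credits that arm with improvement that did not occur. If the control arm is scored too high, the error runs the other way.

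The reason given for unblinded rating does not require unblinding at T0. A nurse can know the resident well without yet knowing a future allocation. Unblinded rating at weeks 6 and 12 may be unavoidable; at T0 it is avoidable.

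**Working it through.** The document gives no figure on this point, so there is none to reproduce. The check has two parts.

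**1. Does the text support the reading?**

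- Recruitment and Participants timeline both go from consent to allocation with no baseline step between them.
- Four scale descriptions call the nurses non-blinded at T0. On its own this could be a formula describing the rater across all visits.
- GDS is harder to explain in that way. Table 1 schedules it at T0 only, yet the text below Fig. 1 calls it unblinded, and Blinding lists dementia stage among the ratings that cannot be blinded. A scale used only at T0 can be unblinded only if the allocation can be known at T0.
- No sentence states the opposite order.
- The text below Fig. 1 mentions the quality-of-life, NPS, agitation and depression questionnaires only at T1b and T2b, whereas Table 1 and Secondary outcomes measures also have them at T0. These places need reconciling.

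**2. How large could the effect be?**

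Inputs from Sample size: correlation between repeated DS-DAT assessments ρ = 0.6; 30 per group; planning SMD 0.32. Assumptions: ρ = 0.6 carries over to the nurse scales; the differential shift s at T0 runs from 0.1 to 0.5 SD; only T0 is shifted; the true effect is zero. The documents give no value for s.

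With equal variances the baseline slope equals ρ, so

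bias = −ρ × s (the arm scored too high at T0 appears to improve).

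For the mean of two follow-ups adjusted for baseline:

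- residual variance = (1 + 0.6)/2 − 0.6² = 0.80 − 0.36 = 0.44, SD = 0.663
- standard error = 0.663 × √(2/30) = 0.171

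| Shift s (SD) | Size of bias, 0.6 × s (SD) | Bias / 0.32 | Type I error |
|---|---|---|---|
| 0 | 0 | 0% | 0.048 (simulated) |
| 0.1 | 0.06 | 19% | 0.064 (normal approximation) |
| 0.2 | 0.12 | 37.5% | 0.104 (simulated) |
| 0.3 | 0.18 | 56% | 0.171 (simulated) |
| 0.5 | 0.30 | 94% | 0.377 (simulated) |

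The simulations used 20,000 trials per scenario, with 30 per arm and a nominal level of 0.05. The mean estimates were −0.119, −0.179 and −0.301 SD for s = 0.2, 0.3 and 0.5, in line with the formula. The ratio to 0.32 is given for scale only, because 0.32 is the planning effect for DS-DAT and not for the nurse scales.

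**If the bias persists.** Let the follow-up ratings shift by k × s in the same arm. The net bias is then (k − 0.6) × s. It is zero at k = 0.6. At k = 1 it is 0.4 × s with the opposite sign. If the nurse's leaning reverses at follow-up (k below 0), the two errors add. Neither the sign nor the size of the net error can be known in advance.

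**The case against.** The strongest objection is that the sequence is inferred. No sentence orders T0 against randomisation, a T0 placed one week before sessions fits either order, and Fig. 1, which shows the participant flow, is missing from the copy reviewed. The exact moment at which allocation is released is also something a journal article may leave to the full protocol. This stands as a limit on certainty. It does not clear the text, which describes unblinded nurse ratings at T0, GDS included. If Fig. 1 places T0 first, that wording is wrong and needs correcting.

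A reader might infer that nurses are shown to know the arm at T0, that allocation follows consent immediately, or that every nurse-rated outcome will show a false benefit. The documents support none of these. They say only that allocation comes after consent, and they give no evidence that any shift occurs, or in which direction.

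A reader might also infer that the primary result is compromised. It is not, on this ground. The DS-DAT baseline has a blinded rater, a crude analysis is planned, and the only route to the primary outcome is GDS, a seven-stage scale, in the adjusted model.

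The safeguards count for something. Nurses are not told the hypothesis, the control visits match the therapy in frequency and duration, and the Discussion acknowledges unblinded secondary outcomes as a limitation. That acknowledgement does not extend to the baselines. NPI-NH is also used to screen for eligibility, but the text does not say whether the screening score serves as T0.

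The numerical objection stands in full: s is assumed, and 0.6 is borrowed from a scale with a blinded rater.

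**Conclusion.** The concern holds for the nurse-rated scales. As the article is written, the T0 values of QUALID, NPI-NH, CMAI and CSDD, and GDS as the likely cognitive covariate, can be influenced by knowledge of the arm, and nothing stated prevents it. The crude analysis of DS-DAT and the PAIC-15 baseline are outside the problem.

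The range of 0.06 to 0.30 SD is an illustration and not an estimate. It rests on an assumed differential shift of 0.1 to 0.5 SD at T0 alone and on a slope of 0.6 carried over from DS-DAT; persistent nurse bias would partly offset it. The case for acting rests less on that size than on the fact that this source of bias is avoidable at very little cost. Removing it would not cure any bias from unblinded rating at follow-up, which the protocol already accepts.

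**What to change.** State the order and follow it: consent, nurse-rated T0 scales (QUALID, NPI-NH, CMAI, CSDD, GDS) completed and logged, allocation released by the statistician, first session. Allocation already describes a statistician who is not involved in carrying out the study in the facilities, so release on confirmation of the logged forms needs no new role.

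Correct the descriptions of nurse ratings in Secondary outcomes measures, in the text below Fig. 1 and in Blinding, so that nurses are unblinded at weeks 6 and 12 only. In the same edit, bring the text below Fig. 1 into line with Table 1 on which questionnaires are completed at T0. If Fig. 1 already shows T0 before allocation, align the text with the figure.

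The cost is that allocation, and therefore session scheduling, comes slightly later. No extra visits or staff are needed. The four outcome scales ask about the preceding one to four weeks, so nurses need no new observation period after consent. DS-DAT, PAIC-15 and actigraphy need not move for this purpose. The MotionWatch is worn for the whole week before sessions start, so placing that week before randomisation would leave no time within it for the therapist to ask about musical preferences and prepare sessions.

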### Assignment of interventions

#### Allocation

Participants will be randomly assigned to either the control or the experimental group with a 1:1 allocation as per a computer-generated randomisation schedule. Randomization is performed by a statistician who is not involved in carrying out the study in the facilities, using randomization software.

#### Blinding

The study is single blinded, i.e. that the therapist and the patients themselves are not blinded. Trained research assistants who are blinded to intervention assignment, conduct the well-being (primary outcome) and pain (secondary outcome) measurements. The nursing staff completes the scales concerning the stage of dementia, QoL, NPS, agitation and symptoms of depression. Blinding to these measurements is not possible because these measurements require familiarity with the person’s usual behavior in the previous week(s). The nursing staff who complete the questionnaires are not blinded to intervention assignment, but they are not informed about the hypothesis and specific research questions.

#### Data analysis

Immediate effects are defined as the difference in change between outcomes 15 min before and after the intervention sessions. Cumulative effects are effects over time not including those immediately after the session (i.e., built-up effect over time and measured before the session in order not to include possible immediate effects of the session). Overall effects are effects over time including those immediately after the session. Immediate, cumulative and overall effects are analyzed with mixed model analysis to consider the dependency of the repeated observations within the patient.

For the immediate effects, the outcome will be the post-test (T1b, T2b) and adjustment will be made for the pre-test (T1a, T2a). For the cumulative effect, the outcome will be the pre-test and an adjustment will be made for the baseline. For overall effects, the outcome will be post-test and adjustment will be made for the baseline.

For all treatment effects, effects at the different time-points will be analyzed by adding a time x treatment interaction to the mixed model analysis. Furthermore, both crude and adjusted (adjustments for gender, age, cognitive deterioration and for medication use, which will be added as a time-dependent covariate) will be performed. In the mixed-model analysis, we will also evaluate whether an adjustment for the correlated observations within facilities is necessary. There is no need to impute missing data because mixed models can handle missing assessments.

In explorative post-hoc analysis we will evaluate whether the intervention effects will be different for patients with a musical background by adding the interaction between the intervention variable and presence of musical background.

Sleep quality data of the MotionWatch (CamNtech Ltd, Cambridge, UK) will be analyzed with Motionware software version 1.2.1. Five parameters will be calculated: Interdaily stability, Intradaily variability, Relative Amplitude, most active period of 10 h and least active period of five hours. The 5 parameters will be analyzed with linear regression analyses with the values measured after the intervention period as outcome with an adjustment for the baseline vale of particular outcome.

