### Sample size

The sample size calculation is based on the study’s primary outcome measure, the Discomfort Scale – Dementia of Alzheimer type (DS-DAT) [51] for F-tests ANOVA repeated measures. To determine the sample size required to assess relevant effects, we used data from the Cochrane review on music-based therapeutic interventions [27]; the effect size for emotional well-being and quality of life (SMD 0.32, 95%CI 0.02 to 0.62). The correlation between multiple assessments of the DS-DAT was calculated with the data of Schalkwijk et al. [57] as 0.6. Using a type I error of 0.05, a power of 0.80, two follow-up measurements and 2 groups, a sample size of 30 in each group is required, totaling 60 participants to achieve 0.81 power. According to the availability of music therapists we estimated that the study would take approximately 3 years. The mortality rate in the nursing home setting is high. Moore [58] stated that the length of stay in long-term care facilities in Europe countries is almost 2 years. It is estimated that about a one third (20 of 60 residents) may die or will be lost to follow up for other reasons during the study period, so we need to enroll a total of around 70 till 80 residents for this study.

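### The plan sets three different treatment effects on the one primary outcome, DS-DAT, and names none of them as the primary test

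*Protocol article*

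**What the plan says.** **Outcome and sample size.** The Sample size section of the protocol article ties the calculation to one scale: "The sample size calculation is based on the study’s primary outcome measure, the Discomfort Scale". It describes a repeated-measures F-test: "Using a type I error of 0.05, a power of 0.80, two follow-up measurements and 2 groups". The result is 30 per group with power 0.81. The section does not say which treatment effect this test addresses.

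**Effects.** The Participants timeline section says DS-DAT is measured "to assess overall effects, cumulative and immediate effects". The Data analysis section states: "Immediate, cumulative and overall effects are analyzed with mixed model analysis". It defines them as follows:

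- Immediate: the value after the session (T1b, T2b), adjusted for the value before it (T1a, T2a).
- Cumulative: the value before the session, adjusted for baseline (T0).
- Overall: the value after the session, adjusted for baseline (T0).

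**Time points and models.** The same section continues: "For all treatment effects, effects at the different time-points will be analyzed by adding a time x treatment interaction". It also plans "both crude and adjusted (adjustments for gender, age, cognitive deterioration and for medication use", with medication use entered as a time-dependent covariate.

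**Ranking.** None is given for the three effects. The only treatment comparison that this section labels exploratory is the interaction with musical background.

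**The concern.** Relief just after a session and a benefit that has built up and is visible before a session are different clinical claims. The plan lets either, or their combination, answer the primary question. The sample size assumes one test at 0.05, but the analysis section offers several and does not say which one that is. A reader of the results could not tell in advance which DS-DAT finding would make the trial positive, and the choice could be made after the results are seen.

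The choice of model matters as well. Medication use over time is measured after randomisation, and psychotropic drug use is itself a secondary outcome. The crude and adjusted estimates may therefore answer somewhat different questions.

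**Working it through.** **1. The plan's own figure.** Inputs from Sample size: effect 0.32, correlation 0.6, type I error 0.05, N = 60, two follow-ups. For the between-group test in a repeated-measures ANOVA with m occasions, the noncentrality is λ = N·f²·m / (1 + (m − 1)ρ), on 1 and N − 2 degrees of freedom.

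- m = 3 (baseline plus two follow-ups): λ = 60 × 0.1024 × 3 / 2.2 = 8.38, power 0.812. This matches the stated 0.81.
- m = 2: λ = 60 × 0.1024 × 2 / 1.6 = 7.68, power 0.778.

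The stated power therefore belongs to one test on one outcome series, whereas Table 1 has five DS-DAT occasions (T0, T1a, T1b, T2a, T2b). The match requires entering 0.32 as Cohen's f. That is a separate matter and does not affect the false-positive rates below.

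**2. Bounds under no effect.** For k independent tests at 0.05, the chance of at least one false positive is 1 − 0.95^k.

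- k = 1: 5.0%
- k = 3: 14.3%
- k = 6: 26.5%

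**3. How far the three effects overlap.** Take one visit with all correlations 0.6. The adjusted outcomes are b − 0.6·T0 (overall), a − 0.6·T0 (cumulative) and b − 0.6·a (immediate), where a is before and b after the session. Each has variance 1 − 0.36 = 0.64.

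- Overall with immediate: (1 − 0.36 − 0.36 + 0.216) / 0.64 = 0.78
- Overall with cumulative: (0.6 − 0.36 − 0.36 + 0.36) / 0.64 = 0.38
- Cumulative with immediate: (0.6 − 0.6 − 0.36 + 0.216) / 0.64 = −0.23

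The effects are far from duplicates, so the joint error should lie nearer 14.3% than 5%.

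**4. Simulation under no effect.** Settings: 30 per arm, five occasions, 6,000 trials, two-sided tests at 0.05. Each test is an ANCOVA with the outcome and adjustment that the plan defines, as an approximation to its mixed models. The last column comes from a second simulation (6,000 to 8,000 trials per setting). It varied the within-session correlation from 0.3 to 0.9, the other correlations from 0.3 to 0.6, and the covariate R² from 0 to 0.30.

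| Success claimed on | All correlations 0.6 | Within-session 0.8 | Second simulation |
|---|---|---|---|
| One named test | 4.9% | 4.9% | about 5% |
| Any of 3 time-averaged effects | 12.1% | 12.2% | 10.8–12.6% |
| Any of 6 time-specific effects | 22.2% | 21.7% | 20.8–21.9% |
| Any of these 9 | 24.1% | 24.2% | 22.7–24.5% |

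The Monte Carlo standard error at 12.1% is √(0.121 × 0.879 / 6000) = 0.4 percentage points.

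**5. Crude and adjusted.** Testing one effect both ways gives about 6% to 7%. Testing the three time-averaged effects both ways gives 14% to 16%. The crude and adjusted versions are strongly correlated, so most of the inflation comes from having three effects and two time points.

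**The case against.** The strongest reply is that this is a journal article whose analysis plan is not shown, and that plan may name the contrast and a testing order. Nor does the article call the three effects co-primary. Each has a stated outcome and adjustment, and the aim can be read as estimating short-term and long-term effects side by side.

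Part of this stands. Multiplicity detail can be left to an analysis plan. However, which contrast answers the primary question is a core protocol element. This article sets out the analysis in detail, lists the contrasts without ranking them, and powers a single test.

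Three stronger readings are tempting, and the document does not support them:

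- **That the plan has a false-positive rate of 12% to 24%.** The level 0.05 appears only as a sample-size input, and no success rule is stated. The percentages hold only under a rule that any significant result counts. The upper end also treats time-specific results as primary claims, although the interaction reads more naturally as a breakdown of each effect.
- **That there are 18 chances of success.** The count 3 effects × 3 time summaries (average, T1, T2) × 2 models describes possible reported results. Crude and adjusted versions of one effect are nearly the same test, and reporting both is routine.
- **That the sample size points to the overall effect.** The cumulative effect also has two follow-ups (T1a, T2a), so the Sample size section does not separate the two.

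**Conclusion.** The point holds in this form: three distinct effects are planned on the single primary outcome, each also by time point and in two models, with none designated primary, while the trial is sized on one test at 0.05.

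Its size depends on a success rule that the article does not give. If any of the three time-averaged effects could carry the claim at 0.05, the risk is about 12% (10.8% to 12.6% over the correlations tried) against 5% for one named test. About 22% to 24% applies only if time-specific results also count. These figures assume no true effect and use ANCOVA in place of the mixed model. They are not sensitive to the assumed correlations.

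Even with no formal inflation, the trial would lack a fixed primary claim, so this should be settled before any analysis by arm.

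**What to change.** State in the protocol, and carry into the analysis plan, one confirmatory contrast, one time summary and one model for DS-DAT.

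- **Contrast and time summary.** One option is the overall effect averaged over T1b and T2b, adjusted for T0. The cumulative effect averaged over T1a and T2a fits the sample-size basis equally well, so the sponsor should choose according to the claim it wants to make.
- **Model.** Adjust for prespecified baseline covariates. This leaves the time-dependent medication covariate out of the primary model. The text should say so openly and keep that model as a supporting analysis.
- **Other effects.** Test the remaining two in a stated order at 0.05, each only if the previous test is significant, or label them secondary.
- **Time-specific and alternative-model results.** Report them as estimates with confidence intervals, without a primary claim.

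The cost is a paragraph of text and no extra participants. The downside is small: if the first test fails, the lower-ranked effects cannot be claimed as confirmatory.
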